#### Data preprocessing

2.7.2

Data preprocessing will be based on recommendations from analytical labs according to the standard practices of each analytical field, data QC assessments, and the planned data analysis approach. Preprocessing may include: (1) corrections for technical effects, which can include between-plate or batch normalizations, (2) removal of contaminants, (3) removal of analytes considered too sparse (too many zero values) or with too many missing values, and (4) missing data imputation algorithms for left-censored data [e.g. using the limits of detection (LOD)], and for randomly missing data. Details and specific examples are provided below.

##### Batch effects

2.7.2.1

Generally when batch effects are suspected, data analysts will follow-up with analytical labs to determine next steps. Using targeted metabolomic data as an example, Biocrates analysts use the HM pool included in each plate to perform a median-normalization to the HM pool on a per-analyte basis to account for inter-plate technical variation. When statistical approaches are insufficient, we will consider re-analysis of samples from a specific batch where technical variation is unacceptably high.

##### Decontaminating HM microbiome data

2.7.2.2

For HM microbiome data, which are prone to contamination issues due to the low biomass of bacteria in HM (86), *Decontam* and *SCruB* algorithms will be used to identify and remove contaminants introduced at both the DNA extraction and sequencing stages (87, 88). These algorithms use information on feature prevalence (88), and batch and position assignment during sequencing to estimate leakage of sequences across samples (87).

##### Missing data—filtering and imputation

2.7.2.3

Missing data issues are prevalent in omics data, stemming from various factors such as cost, poor sample quality, inadequate sample volume, instrument or assay detection limitations, or other experimental factors. Based on the mechanisms producing missing values, these unrecorded data can be further classified as missing not at random (MNAR) or missing at random (MAR) (89). Missing data can be imputed, or the entire feature can be removed.

To avoid introducing large biases when minimal data are available for a given analyte/feature, we will implement preliminary feature- or sample-filtering for specific data types based on standard practices of analytical fields, with consideration for planned downstream analyses. Generally across all study sites and modalities, if over 30% of a feature’s values are considered MAR within any time-point and arm, the feature will be removed.

For targeted metabolomic data, rather than completely removing features with few non-missing values, features with more than 20% of values below the LOD in any given time-point and intervention arm will be binarized across all sites, such that they are retained in the machine learning analysis as it can handle binary features. For untargeted metabolomic data, only metabolites with high alignment confidence between batches (based on mass to charge ratios) will be used in the integrated analysis.

For HM microbiome data, we previously found a depth of 8,000 reads to be sufficient to capture the diversity of HM microbiota (27). Samples with fewer reads are typically removed from analysis. For the current study, this threshold will be relaxed to 1,000 reads to maximize sample retention for integrated analysis. However, to account for the expected lower accuracy of community composition estimates for samples with low read count, an indicator variable identifying samples with fewer than 8,000 reads will be used for adjustment. Further, only microbial features present in over 10% of samples in each site and at each time-point will be included.

After the sample- and feature-filtering described above, any remaining missing values will be imputed. To impute left- and right-censored MNAR data that are missing due to being below or above the limit of detection (LOD) of a given assay, respectively, we will generally follow recommendations from the responsible analytical lab. For microbiome data, zero values (considered left-censored MNAR) will be imputed using Bayesian-multiplicative replacement (90). For untargeted metabolomics data and targeted protein data, left-censored missing values will be imputed by following a uniform distribution with the lower bound set to one-tenth of the minimum observed value and the upper bound to the minimum observed value. Targeted protein values above the detection range (right-censored) will be imputed using a log normal distribution. For targeted metabolomics data, values below the LOD will be imputed using logspline density estimation (91), and using consensus LOD values across plates within each batch. Further, we will interpolate values considered to be MAR with a non-parametric multivariate model based on random forests using the *MissForest* package (92). At each iteration, every feature with existing blank entries will be taken as the outcome predicted by other features. This methodology allows for the elucidation of nonlinear relationships between features, leveraging the interconnected dependencies inherent in biomolecular entities.

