**Methods and analysis:**

IMiC is a collaboration of HM experts, data scientists and four mother-infant health studies, each contributing a subset of participants: Canada (CHILD Cohort, *n* = 400), Tanzania (ELICIT Trial, *n* = 200), Pakistan (VITAL-LW Trial, *n* = 150), and Burkina Faso (MISAME-3 Trial, *n* = 290). Altogether IMiC includes 1,946 HM samples across time-points ranging from birth to 5 months. Using HM-validated assays, we are measuring macronutrients, minerals, B-vitamins, fat-soluble vitamins, HM oligosaccharides, selected bioactive proteins, and untargeted metabolites, proteins, and bacteria. Multi-modal machine learning methods (extreme gradient boosting with late fusion and two-layered cross-validation) will be applied to predict infant growth and identify determinants of HM variation. Feature selection and pathway enrichment analyses will identify key HM components and biological pathways, respectively. While participant data (e.g., maternal characteristics, health, household characteristics) will be harmonized across studies to the extent possible, we will also employ a meta-analytic structure approach where HM effects will be estimated separately within each study, and then meta-analyzed across studies.

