##### Data transformations

2.7.2.4

Data transformations will generally not be performed given the use of a late fusion model, where each individual model is designed to handle different data distributions independently. Exceptions include the binarization of some features with few non-missing values as described above, and a centered-log ratio (CLR) transformation of microbiome features, used to account for the compositionality issue of sequencing data (93).

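### A single arm-by-time cell with more than 20% of values below LOD binarises a targeted metabolite in all four studies, although the rule is meant for features with little data

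*Protocol article*

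**What the plan says.** Section 2.7.2.3 (Missing data—filtering and imputation) fixes the rule for targeted metabolites: "features with more than 20% of values below the LOD in any given time-point and intervention arm will be binarized across all sites". It sets no minimum cell size, no condition at study level and no exception for a study in which the metabolite is well detected. The stated reason is to keep such features in the machine learning analysis, "rather than completely removing features with few non-missing values". Section 2.7.2.4 (Data transformations) says that transformations are generally not needed with the late fusion model and lists this one as an exception: "Exceptions include the binarization of some features with few non-missing values as described above".

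For features that pass the filters, section 2.7.2.3 plans another treatment: "For targeted metabolomics data, values below the LOD will be imputed using logspline density estimation (91". Section 2.1 plans to estimate effects within each study and then meta-analyse them, and section 2.7.1.3 adds site-specific analyses.

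**The concern.** The trigger and the purpose do not match. A cell with 11 of 50 values below LOD still has 39 of 50 detected (78%), which is not a feature with few values. The decision is taken in the smallest unit of the data but applied to the largest.

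The article does not state where the binary cut lies. If it is detected versus not detected, a study that detects the metabolite in every sample is left with a constant, and a study that detects it in nearly every sample is left with a near-constant. The quantitative measurement is discarded in the studies where it was best. What is at stake is the within-study growth associations that feed the meta-analysis. In a pooled model such a binary may also largely mark site or arm, which is the confounding that section 2.7.1.3 sets out to control.

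**Working it through.** **Inputs from Table 2 (actual samples).** CHILD 399 at one time-point, no arms. ELICIT 200 + 200, four groups of 50. VITAL-LW 150 + 150, three groups of 50. MISAME-3 276, 287 and 283, four groups, so about 69 to 72 per cell. The article gives no below-LOD rates, so those used here are assumptions shown as ranges.

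**Reproducing the plan's figure.** 399 + 200 + 200 + 150 + 150 + 276 + 287 + 283 = 1,945, against the 1,946 in the abstract ("Altogether IMiC includes 1,946 HM samples across time-points ranging from birth to 5 months"). The difference of one has no bearing here.

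**Cells.** 1 + 4×2 + 3×2 + 4×3 = 27, of which 8 + 6 = 14 have 50 samples.

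**Trigger count**, floor(0.2n) + 1: 11 of 50 in ELICIT or VITAL-LW, 14 or 15 of 69 to 72 in MISAME-3, 80 of 399 in CHILD. The smallest share that can recode a metabolite everywhere is 11/1,945 = 0.57%, leaving 99.4% of values detected.

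**Chance that at least one cell triggers.** 1 − Π[1 − P(X ≥ trigger)], X binomial(n, p), cells independent. The last column applies the same 20% threshold to each study's pooled samples.

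| True below-LOD rate, all cells | One cell of 50 | Any of 27 cells | Any study, pooled over its cells |
|---|---|---|---|
| 10% | 0.9% | 18% | <0.1% |
| 12% | 3.2% | 53% | <0.1% |
| 15% | 12% | 96% | 1.4% |

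The excess comes from the single-cell trigger, not from the 20% figure alone.

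**Variation between cells (beta-binomial), mean rate 5%.** No variation: below 0.1%. Intraclass correlation (ICC) 0.01: about 2.4%. ICC 0.02: 11%. ICC 0.05: 46%. The last implies a between-cell standard deviation of √(0.05×0.95×0.05) = 4.9 percentage points, as large as the mean.

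**Information kept by a cut at the LOD.** For a normally distributed measurement with a fraction p below the cut, this is φ(z_p)²/[p(1−p)].
- p = 5%: 0.1031²/0.0475 = 0.22
- p = 2%: 0.0484²/0.0196 = 0.12
- p = 0: zero, because the variable is constant

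**Illustration in CHILD (n = 399).** Assume a correlation of 0.2 with growth. The cut multiplies it by a = φ(z_p)/√[p(1−p)], and power is Φ(atanh(0.2a)·√396 − 1.96). It is 98% on the continuous value, 47% at 5% below LOD (a = 0.473), 28% at 2% (a = 0.346) and 19% at 1% (a = 0.268, about 4 of 399 in the minority class). This is a linear test and not the boosted-tree model; it shows the scale of the loss only.

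**Dependence on arm.** Take VITAL-LW's six cells with a mean rate of 10%. A uniform 10% triggers with probability 5%. A rate of 20% in the control arm and 5% in the two supplemented arms (mean (2×20 + 4×5)/6 = 10%) triggers with probability 66%. ELICIT's infant antimicrobials start at 6 months (section 2.1.2), after both milk samples, so its four groups are two maternal exposures split into smaller cells, which makes chance triggers more likely.

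**The case against.** **The rule keeps features.** A reader might infer that setting-specific metabolites are filtered out. They are not: binarising is the article's alternative to removal, and a metabolite detected in one country but not in another survives as a binary.

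**Supplement-responsive metabolites.** A reader might infer that these are hit first. The documents give no detection rates by arm. A metabolite with 30% below LOD everywhere and no response triggers with near certainty, and a responsive one well above the LOD is untouched. What stands is that, at an equal overall rate, the rule can preferentially affect metabolites whose detectability differs by arm or site.

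**Scope.** Section 2.7.2.3 ties the rule to machine learning. Section 2.9.3 does not say that binarised versions enter the intervention analysis, where targeted metabolomics are tertiary outcomes. Harm there cannot be asserted. Nor does a metabolite drop out of the meta-analysis altogether: only a study with no value below LOD yields a constant, and the others still contribute.

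**Imputation and common coding.** Imputation follows filtering, so the logspline step is planned only for features under the threshold, and reluctance to impute a heavily censored block is reasonable. One coding across sites also serves the aim in section 2.4.3 of analysing all sites together. Both points are fair, but neither calls for a single-cell trigger: 22% below LOD in one cell is not heavy censoring of the feature, and continuous values plus an indicator are also a common coding.

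**Assumptions.** The same women recur across time-points in three studies, so the cells are not independent. The supplementary analysis plan is not shown and may state the cut.

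**Conclusion.** The point holds for the rule as written. A 20% non-detection rate in one cell of 50 is a poor marker of a feature with few values, and applying the result to all four studies can leave a metabolite uninformative where it was well measured. Triggers are likely when the below-LOD rate is about 12% or more everywhere (53% at 12%, 96% at 15%). At a 5% mean rate they are rare unless cells differ materially.

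The trigger probabilities rest on assumed rates and independent cells; the information figures rest on a normal measurement and a cut at the LOD. The conclusion concerns targeted metabolites in the machine learning and within-study estimates. The removal rule for values missing at random and the microbial prevalence filter in the same section are separate rules and not part of this point.

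**What to change.** - For targeted metabolites, keep continuous values in all four studies, with below-LOD values imputed by the logspline method already planned, and add a detected/not-detected indicator. Tree models then have at least the information that the binary gives, and the coding stays common for pooling.
- Drop the single-cell trigger. Assess non-detection per study, pooled over arms, and rely on the indicator alone only where most values in that study are below LOD. The exact cut-off is a convention; fix it before the analysis.
- State where the binary cut lies.
- State whether the rule also applies to the intervention analysis in section 2.9.3.

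The cost is a few lines of preprocessing code, one paragraph of text and one extra indicator column per affected metabolite. A few features will be informative only as a binary in some studies.

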#### Intervention effects analysis

2.9.3

We will also estimate the effects of randomized interventions on human milk components in the three intervention studies. Two different definitions of ‘milk composition’ will be used (1) individual milk components, adjusted for multiple testing and (2) predictive summary measures calculated from milk biomarkers of infant growth using targeted learning and other dimension reduction techniques (96). We will estimate both unadjusted and covariate-adjusted intervention effects on each HM outcome, adjusting for baseline prognostic factors using cross-validated targeted maximum likelihood estimation (97). In addition to analyzing HM components at each time point, we will also examine changes in HM components between timepoints. We will correct for multiple comparisons by using the Benjamini-Hochberg procedure, and group corrections by time-point and outcome group. Primary outcomes are macro- and micro-nutrients, secondary outcomes are HMOs and targeted proteins and bioactives, tertiary outcomes are targeted metabolomics, and exploratory outcomes and untargeted metabolomics, untargeted proteomics, and the microbiome.

As a secondary analysis, we plan to assess the potential mediating effects of HM components on the relationship between maternal nutritional supplementation or other maternal factors, and infant growth outcomes (Supplementary material).

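### On the text as written, milk outcomes in the randomized comparisons would be filled once by MissForest, with arm not named as a predictor, and analysed as if observed

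*Protocol article*

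**What the plan says.** The Protocol article describes one curation route for the milk data, in Section 2.7.

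- **Filter** (2.7.2.3), stated generally for all sites and modalities: "if over 30% of a feature’s values are considered MAR within any time-point and arm, the feature will be removed". A feature at or below that share stays in.
- **Imputation** (2.7.2.3): every value still missing after the filters is to be filled. Values beyond detection limits have their own methods. For the rest, "we will interpolate values considered to be MAR with a non-parametric multivariate model based on random forests using the" MissForest package, and "At each iteration, every feature with existing blank entries will be taken as the outcome predicted by other features". Arm is neither named nor excluded as a predictor, and multiple imputation is not mentioned.
- **Scale** (2.7.2.4): "Data transformations will generally not be performed given the use of a late fusion model", apart from some binarized features and the log-ratio transformation of microbiome data.
- **Use as trial outcomes** (2.9.3): "We will estimate both unadjusted and covariate-adjusted intervention effects on each HM outcome", the adjusted ones by cross-validated targeted maximum likelihood estimation (TMLE). Macro- and micronutrients are primary. The section names no other data set, no rule for missing outcomes and no analysis scale.

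Section 2.7.2 also says that preprocessing takes account of "data QC assessments, and the planned data analysis approach".

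**The concern.** Filling gaps in a predictor is ordinary practice for a prediction model. Filling gaps in a trial outcome and then treating the filled values as measured is different. If the forest does not know the arm, the filled values carry a between-arm difference only to the extent that other milk features do. The effect on the component itself is then mixed with whatever the other features do. One completed data set also hides the uncertainty of the filled values.

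At stake is objective 3 of the consortium, the effect of maternal nutritional interventions on milk composition. It is answered by comparing randomized groups in three trials, with groups of 50 to about 75 dyads.

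**Working it through.** The article gives no power, effect size, SD or significance level for Section 2.9.3, so there is no figure of its own to reproduce.

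**Inputs from the document**
- Largest MAR share still imputed: 30% per time-point and arm (2.7.2.3).
- Group sizes: ELICIT 50, VITAL-LW 50, MISAME-3 about 75 (Table 2).
- Whole-sample loss (Table 2): ELICIT 200 of 200 at both visits and VITAL-LW 150 of 150 at both visits, so 0%. MISAME-3 has 276, 287 and 283 of 290, so 14/290 = 4.8%, 3/290 = 1.0% and 7/290 = 2.4%.

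**Assumptions**
- True effect δ = 0.566 SD and two-sided 5% level. With 50 per arm, δ√(n/2) = 0.566 × 5 = 2.83, and Φ(2.83 − 1.96) = 0.81 power with complete data.
- Ten other features, with pairwise correlation 0.5 among themselves and with the outcome.
- Values missing completely at random; one random-forest imputation without arm; then a t-test.
- 1,200 runs per row. The Monte Carlo standard error is √(0.83 × 0.17/1200) = 1.1 points at 83% coverage and 0.6 points at 95%.

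**Expected bias.** With missing share m and an average between-arm difference Δ in the filled values, the expected estimate is (1 − m)δ + mΔ. If the correlated features do not respond to the intervention, Δ is near 0 and the estimate is about (1 − m)δ. If they respond, Δ follows them, whatever δ is.

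**Simulation, 50 per arm.** Triples are estimate / 95% coverage / rejection rate.

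| MAR share | δ | Shift in other features | (1 − m)δ | Imputed | Observed values only |
|---|---|---|---|---|---|
| 5% | 0.566 | 0 | 0.538 | 0.533 / 94.1% / 77.7% | 0.562 / 94.5% / 78.3% |
| 10% | 0.566 | 0 | 0.509 | 0.505 / 93.6% / 74.3% | 0.563 / 94.6% / 76.3% |
| 20% | 0.566 | 0 | 0.453 | 0.445 / 90.6% / 65.5% | 0.562 / 94.5% / 70.5% |
| 30% | 0.566 | 0 | 0.396 | 0.389 / 83.0% / 56.5% | 0.562 / 95.7% / 63.7% |
| 30% | 0.566 | 0.566 | – | 0.520 / 94.0% / 82.4% | 0.562 / 95.7% / 63.7% |
| 30% | 0 | 0.566 | – | 0.109 / 90.6% / 9.4% | −0.004 / 95.7% / 4.3% |
| 30% | 0 | 0 | 0 | −0.005 / 95.7% / 4.3% | −0.004 / 95.7% / 4.3% |

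**Reading the rows**
- In the first four rows the estimate follows (1 − m)δ closely. Shrinkage is 1 − 0.533/0.566 = 6% at 5% missing and 1 − 0.389/0.566 = 31% at 30%.
- Where all features shift equally, the filled values carry Δ ≈ (0.520 − 0.396)/0.3 = 0.41, so little is lost.
- Where only the other features shift, Δ ≈ 0.109/0.3 = 0.36, and a component with no effect acquires one.
- Where nothing responds, there is no harm.

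**Variations at 30% missing, other features not shifted**
- Correlation 0.2 instead of 0.5: 0.392, coverage 83.3%.
- 145 per arm (290/2, half of MISAME-3) with δ = 0.33: 0.228 against 0.7 × 0.33 = 0.231, coverage 84.1%.
- Arm added as one more predictor in the single forest: 0.422, coverage 85.3%. This does not repair the problem.

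**The case against.** The strongest reply is that the article does not say the imputed file feeds Section 2.9.3, nor that arm is left out of the forest. Preprocessing is said to depend on the planned analysis. Binarized metabolites "will be binarized across all sites, such that they are retained in the machine learning analysis as it can handle binary features", and transformations are waived for a reason specific to late fusion. Missing-outcome rules are commonly left to an analysis plan, and TMLE can accommodate missing outcomes. This stands as a limit on certainty. It does not remove the point, because the imputation rule is stated for all remaining missing values and nothing exempts the trial outcomes.

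The second reply is about size. The 30% figure is a removal cap, not an expected rate, and whole-sample loss is at most 4.8%. At 5% missing, coverage is 94.1% against 94.5%, which is within simulation error. This also stands, although whole-sample counts do not bound the loss for a single analyte: Section 2.7.2.3 itself lists inadequate volume, cost and assay limits as causes.

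The third is that the comparison favours observed values, since the simulation made missingness completely random. If missingness depends on co-measured milk features, a model using only arm and baseline covariates can itself be biased. That was not tested, and it is why the multiple-imputation option below includes those features.

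A reader might also infer two stronger claims that the document does not support:
- **That intervention effects are generally shrunk.** Direction and size depend on how correlated features respond. Joint response is plausible in ELICIT, for example, where mothers receive nicotinamide and several related B3 compounds are measured together.
- **That a log scale is required.** The raw mean difference is a valid estimand, a geometric mean ratio is a different one, and no analyte distribution is documented. With lognormal data, 50 per arm and a ratio set for about 80% power on the log scale, raw-scale power is 77.5% at an assumed log-SD of 0.3, 67.1% at 0.8 and 59.9% at 1.0. That is lost precision, not bias.

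**Conclusion.** The point holds in conditional form. Followed as written, Sections 2.7.2.3 and 2.9.3 lead to testing singly imputed outcomes as though they were measured. If that is done, bias runs toward zero by about the missing share when correlated features do not respond, is small when they respond equally, and runs away from zero when only they respond (type I error 9.4% at 30% missing). When the component responds and its correlates do not, coverage is about 83–85% at the cap and about 94% at 5% missing.

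These figures rest on the assumed effect, correlations and completely random missingness, and on a t-test in place of the cross-validated TMLE, without the Benjamini-Hochberg step. The actual MAR shares are not given, so the harm may be slight for many components. The change is worth making because it is cheap and the affected comparisons are randomized. The late-fusion reason for leaving data untransformed does not apply to Section 2.9.3, so the scale there needs its own justification. A log scale is an option for strongly skewed analytes, not a correction the plan must make.

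**What to change.** State in Section 2.9.3 that MAR milk outcomes are not filled by the MissForest step, and choose one of two routes:

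1. Analyse observed values, with missingness handled in the planned TMLE through a model using arm and baseline covariates.
2. Use multiple imputation that includes arm, baseline covariates and co-measured milk features. This is preferable where missingness may depend on other milk features.

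MissForest can remain for the prediction models in Section 2.9.2. Adding arm to a single forest imputation is not enough. State also the analysis scale for Section 2.9.3 by analyte group, with a reason that belongs to that analysis. Reporting the MAR share per component, time-point and arm would let readers judge how much the choice matters.

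The cost is about a paragraph of text, a separate un-imputed analysis file, and numbers of observations that differ between components.
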